### Statistical analysis

Analysis will be carried out by the software SPSS 16 (SPSS Inc. Chicago, Illinois), separately for each group of subjects and across groups.

Descriptive analysis will be used to check the distribution of the data. Bivariate analysis will be used to compare within each group the characteristics of experimental and control groups, by chi-square for frequencies and *t* test for continuous variables. Paired tests will be used to check for the variation in cognitive measures before and after intervention within each group. General linear models will be used to verify the effect of intervention in the outcome measures, adjusting for covariates.

Each subject will be classified on the basis of primary outcomes and then included in multiple logistic regression models to identify the predictors of improvements in cognitive status, adjusting for covariates. Repeated-measures ANOVA will be used to examine the training effect on biochemical parameters adjusted for age and sex. The significance level will be set at *P* < 0.05.

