**Methods:**

The study is a prospective randomized intervention for the assessment of cognitive training effects in three groups of elderly subjects with different cognitive status. A total of 321 elderly people were enrolled in Marche Region, Italy. Each subject was randomly assigned to an experimental group or to a control group. Cognitive performances and biochemical blood markers have also been analysed before cognitive training (baseline), immediately after termination (follow-up 1), after 6 months (follow-up 2) and after 2 years (follow-up 3).

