### Sample size calculation

It was based on the null hypothesis that proportion of “success” and “failure” to the intervention is equal in the two groups of subjects (i.e. EG and CG), such as OR = 1.

Success and failure were defined differently for each group of subjects (i.e. HE, MCI, AD) on the basis of a significant variation in the primary outcomes (see below).

Considering an OR = 1.5 indicative of an effect of cognitive training, a total sample of 300 subjects (i.e. 100 subjects per group) allow to reach a 90 % of statistical power using logistic regression at the 5 % level (two-tailed). Drop-out rate was set at 20 %; indeed, a total of 321 subjects were recruited.

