### Secondary outcomes

They includeThe assessment of the effects of intervention and the relationship between psychological status, lifestyle characteristics, functional and health status, biochemical aspects by the use of a multidisciplinary approach.The investigation of rate of percentage of subjects with MCI who converted to dementia.The identification of biochemical markers correlated with the cognitive training in HE, MCI, AD.

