### Blood sample collections

Blood is drawn from the cubital vein between 8:00 and 9:00 AM, in fasting state. A total of thirty millilitres of blood was drawn from each individual at baseline and at each phase of FU. The blood is divided as shown in Fig. 2. Plasma cortisol, ACTH, vitamin B12, folic acid, albumin and creatinine have been assessed.

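### The biomarker model adjusts for age and sex but not for each marker's own baseline value, which costs precision in the EG–CG contrast at each visit

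*Protocol article*

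**What the plan says.** The Statistical analysis section names both the model and the adjustment for the markers: "Repeated-measures ANOVA will be used to examine the training effect on biochemical parameters adjusted for age and sex". No other covariate is listed there. The section gives an alpha of 0.05 and says that analyses are run within each cognitive group and across groups.

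The baseline value exists for every subject. The section on blood sample collections says: "A total of thirty millilitres of blood was drawn from each individual at baseline and at each phase of FU". The abstract dates the three follow-ups: "immediately after termination (follow-up 1), after 6 months (follow-up 2) and after 2 years (follow-up 3").

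The analysis serves a listed secondary outcome: "The identification of biochemical markers correlated with the cognitive training in HE, MCI, AD". The article gives no power, effect size, standard deviation or between-visit correlation for any marker.

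**The concern.** In a randomised comparison of a continuous measure, the subject's own pre-treatment value is usually the strongest predictor of the later value. The article leaves it out of the adjustment although it is already collected. There are two ways to read the sentence.

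- **Baseline is one of the repeated levels.** It is then treated as an outcome. The group-by-time test, taken at any one follow-up, is a comparison of change from baseline. The group main effect would average in a visit at which randomised arms differ only by chance.
- **Only the follow-ups are levels.** The marker's baseline is then not used at all.

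Neither reading uses baseline as efficiently as covariate adjustment does. The cognitive groups hold 111, 109 and 101 subjects, so about 50 per arm if allocation is 1:1. At that size the loss can decide whether a real marker response is detected.

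**Working it through.** **No figure in the article to reproduce.** The only power statement, "a total sample of 300 subjects (i.e. 100 subjects per group) allow to reach a 90 % of statistical power", concerns the binary primary outcome at an odds ratio of 1.5. Whether it holds is a separate question, and nothing below depends on it.

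**Inputs from the article**
- Four blood draws: baseline and three follow-ups.
- About 100 subjects per cognitive group.
- Alpha 0.05. Sidedness is not stated for the markers. Two-sided is assumed, as in the sample size section ("using logistic regression at the 5 % level (two-tailed")).
- Planned drop-out of 20%.

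**Assumptions, because the article gives no value**
- 1:1 allocation, so n = 50 per arm (40 after 20% drop-out).
- Effect d = 0.4 SD at the visit tested.
- Equal variance at all visits and equal correlation ρ between visits, varied.
- Age and sex left out of all models alike.

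**Step 1: variance factor v for one visit, in units of SD²**
- Unadjusted follow-up value: v = 1.
- Change score: v = 2(1−ρ).
- Baseline-adjusted: v = 1−ρ² = (1−ρ)(1+ρ).

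Since 1+ρ < 2 whenever ρ < 1, the adjusted variance is below that of the change score for every ρ < 1. It is below 1 for every ρ other than 0. The direction therefore does not rest on an assumed ρ.

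**Step 2: single-visit power.** z = d / √(2v/n), power ≈ Φ(z − 1.96), n = 50. Example at ρ = 0.5:
- Change score: v = 1.00, z = 0.4/√0.04 = 2.00, power 51.6%.
- Adjusted: v = 0.75, z = 0.4/√0.03 = 2.31, power 63.7%.

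| ρ | Unadjusted | Change score | Baseline-adjusted | Loss v change score | Loss v unadjusted |
|---|---|---|---|---|---|
| 0.3 | 51.6% | 39.4% | 55.4% | 16 | 4 |
| 0.5 | 51.6% | 51.6% | 63.7% | 12 | 12 |
| 0.7 | 51.6% | 73.3% | 80.0% | 7 | 28 |
| 0.8 | 51.6% | 88.5% | 91.5% | 3 | 40 |

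With 40 per arm, change score against adjusted is 32.7% v 46.6%, 43.2% v 54.2% and 63.7% v 70.7% at ρ = 0.3, 0.5 and 0.7.

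**Step 3: pooled across groups.** With about 150 per arm and the same effect, change score against adjusted is 83% v 95%, 93% v 98% and 99.4% v 99.8% at ρ = 0.3, 0.5 and 0.7. The loss is smaller at each of these values.

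**Step 4: does averaging follow-ups 1–3 do better still?** That depends on the shape of the effect. Take ρ = 0.5 and n = 50.
- Averaged, baseline-adjusted contrast: v = (1+2ρ)/3 − ρ² = 0.667 − 0.25 = 0.417, so the standard error is √(2 × 0.417/50) = 0.129.
- Group-by-time F test over four visits (3 and 294 df): noncentrality λ = (n/2) Σ(eₖ − ē)²/(1−ρ), where eₖ is the effect at visit k.

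*Constant effect of 0.4 SD at all follow-ups.* Averaged contrast: z = 0.4/0.129 = 3.10, power 87%. Group-by-time: λ = 25 × 0.12/0.5 = 6.0, power 51%.

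*Effect fading as 0.4, 0.2, 0 SD.* Averaged contrast: z = 0.2/0.129 = 1.55, power 34%. Group-by-time: λ = 25 × 0.11/0.5 = 5.5, power 47%. The ranking reverses. The baseline-adjusted contrast at follow-up 1 alone keeps the 64% of step 2.

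**The case against.** **The planned method is valid and suits the aim.** The introduction asks about changes in markers before and after the intervention, and a group-by-time test addresses that. This stands. A reader might infer that the planned analysis is biased or unusable. It is not: with randomised arms, both readings of the sentence estimate the training effect without bias. Chance baseline differences add noise, and baseline adjustment removes part of it.

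**The loss could be small.** This also stands. The article states neither ρ nor an effect size, so no single figure can be given as fact. Against the change score the loss nearly vanishes at high ρ, and it is smaller when the cognitive groups are pooled. Against an unadjusted follow-up value it moves the other way and grows with ρ.

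**A reader might infer that the loss is larger over all visits, so that an averaged follow-up contrast is always better.** The article does not support this. Training lasts about 2 months and the last follow-up comes at 2 years, and nothing says that the effect stays constant. Part of any all-visit gain also comes from replacing a 3-df test with a 1-df contrast, which has nothing to do with baseline. Only the single-visit comparison isolates baseline adjustment.

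**The article is condensed.** Its sentence on general linear models mentions unlisted covariates, and a fuller plan may give more. But that sentence concerns the outcome measures generally. The marker sentence is separate and names its own model and two covariates. What is left open is which visits are levels and which test counts, and both readings fall short of covariate adjustment.

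**Conclusion.** The point holds as one of precision on a secondary outcome. The stated adjustment set omits the marker's baseline value, and at any given visit the EG–CG contrast is less precise than the baseline-adjusted one: variance 1−ρ² against 2(1−ρ) or 1.

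Within one cognitive group, the cost against a change score is about 16, 12, 7 and 3 power points at ρ = 0.3, 0.5, 0.7 and 0.8. Against an unadjusted follow-up value it is about 4, 12 and 28 points at ρ = 0.3, 0.5 and 0.7. These sizes rest on assumed 1:1 allocation, 50 per arm, a 0.4 SD effect and a two-sided 5% test. The direction rests on none of them, except that ρ must be below 1 for the change score and other than 0 for the unadjusted value. No general claim about power over all visits follows.

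**What to change.** Replace the marker sentence in the Statistical analysis section with wording such as:

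> For each biochemical parameter, the EG–CG difference will be estimated from a repeated-measures model of follow-ups 1–3 with group, visit and group-by-visit terms, adjusted for the baseline value of that parameter, age and sex. The difference will be reported at each follow-up, with follow-up 1 (end of training) as the main contrast.

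Baseline thereby moves from the within-subject levels, if it was one, to the covariates. The visit-specific differences must stay. A difference averaged over follow-ups 1–3 should not be the only result, because it can have less power than the planned group-by-time test if the effect has faded by 2 years.

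The cost is one sentence and one degree of freedom per marker, with no new data or subjects. The general linear model procedure for repeated measures in the software already named can fit it. One downside is that a subject without a valid baseline assay does not contribute to that marker's model. If baseline was already a repeated level in a complete-case analysis, such a subject was excluded anyway.

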### Monocyte isolation, RNA extraction, expression profiling and data analysis

Total RNA was extracted from the monocytes using the RNeasy Mini Kit (Qiagen, Hilden, Germany) as recommended by the manufacturer. Purified RNA was quantified using a NanoDrop spectrophotometer, and RNA integrity was determined by gel electrophoresis. The microarray procedure was performed according to the Affymetrix protocols (Santa Clara, CA, USA). Hybridization cocktails containing fragmented, end-labelled single-stranded cDNA were prepared and hybridized to GeneChip Human Exon 1.0 ST arrays (Affymetrix, Santa Clara, CA, USA). Washing and scanning were performed using GeneChip^®^ Fluidics Station 450 and GeneChip^®^ Scanner 3000 7G (Affymetrix Inc.) and converted to numerical data using GeneChip^®^ Command Console^®^ Software (AGCC). The microarray data analysis will be performed by Partek Genomics Solution 6.6 software (http://www.partek.com). The robust multi-array analysis (RMA) of Irizarry et al.’s algorithm will be used for probe set (exon-level) intensity analysis. Exon-level data will then be filtered to include only those probe sets that are in the “core” meta-probe list, which represents 17 800 RefSeq genes and full-length GenBank mRNAs. Within this gene set, the analysis of variance (ANOVA) and multi-test correction for *P* values in Partek Genomic Suite will be used to identify alternative splicing events. A list of genes with significant alternative spliced events will be generated by using a 0.05 FDR criterion as a significant cut-off. The genes will be sorted based on gene function using Partek Pathway software.

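### Repeated-measures ANOVA on the blood markers loses anyone who misses a draw if all four draws enter; a mixed model keeps them, and the flat 0.05 level needs FDR control or an exploratory label

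*Protocol article*

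**What the plan says.** The Statistical analysis section of the protocol article names the method for the blood markers: "Repeated-measures ANOVA will be used to examine the training effect on biochemical parameters adjusted for age and sex". It then gives one general level: "The significance level will be set at *P* < 0.05". Analyses are run "separately for each group of subjects and across groups".

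On timing, the Blood sample collections section says: "A total of thirty millilitres of blood was drawn from each individual at baseline and at each phase of FU". The abstract places the three follow-ups directly after training, at 6 months and at 2 years. The Sample size calculation section sets drop-out at 20% and reports 321 subjects recruited.

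On the aim, one of the secondary outcomes is: "The identification of biochemical markers correlated with the cognitive training in HE, MCI, AD".

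A multiplicity rule appears in one place only, for the monocyte arrays: "A list of genes with significant alternative spliced events will be generated by using a 0.05 FDR criterion as a significant cut-off".

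The article does not list which markers or which visits enter the ANOVA, and it gives no number of marker tests.

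**The concern.** Classical repeated-measures ANOVA needs a complete row for each subject. A person who gives blood at baseline, after training and at 6 months but not at 2 years would be removed entirely for that marker. The follow-up 1 value, taken right after training, would go too. In a 2-year study of older people, many with MCI or AD, missed draws are to be expected, and the plan itself allows for 20% drop-out. The stakes are lost precision at the earlier visits, and results that describe only those who completed 2 years.

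The second matter is the error rate of a search for markers. Many analytes are measured and analysed in three groups and also across groups, against a single 0.05 level. The Discussion says that health programmes will be outlined on the basis of the findings, so a few chance markers could carry weight.

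**Working it through.** **Plan's own figure.** The article states no power, test count or error rate for the markers, so there is nothing to reproduce on this point. The usable inputs are the 20% drop-out, the 321 recruited (111 HE, 109 MCI, 101 AD), the four draws and the 0.05 level.

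**1. Subjects left with all four draws**

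- Overall: 321 × 0.8 = 256.8, about 257.
- By group: HE 111 × 0.8 = 88.8; MCI 109 × 0.8 = 87.2; AD 101 × 0.8 = 80.8.

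**2. Cost at follow-up 1.** The standard error scales with 1/√n. If all drop-out happens after follow-up 1, every subject has that value but only 80% are used. The ratio is 1/√0.8 = 1.118, about 12% larger. If some leave before follow-up 1, the avoidable loss there is smaller, so 12% is an upper figure for 20% drop-out alone.

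The sample size section supports a milder figure as well. The target of 300 out of 321 allows a loss of only 1 − 300/321 = 6.5%, and the ratio is then √(321/300) = 1.034.

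**3. Sporadic missed draws (assumed rates).** Suppose each follow-up is missed independently at rate m and baseline is always present. The share with all four draws is (1 − m)³. Among those with a follow-up 1 draw, the share kept is (1 − m)², so the standard error ratio at that visit is 1/(1 − m).

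| m | All four draws | SE ratio at follow-up 1 |
|---|---|---|
| 5% | 86% | 1.05 |
| 10% | 73% | 1.11 |
| 20% | 51% | 1.25 |

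**4. Number of marker tests.** The laboratory sections describe nine focal measures: BDNF mRNA, plasma BDNF, tPLA2, APP ratio, d-ROMs, zinc, copper, iron and selenium. Six routine analytes are also measured: cortisol, ACTH, vitamin B12, folic acid, albumin and creatinine. With k tests at 0.05 and no true effects, the expected number of false positives is 0.05k. The chance of at least one is 1 − 0.95^k if tests are independent.

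| Count | k | Expected | At least one |
|---|---|---|---|
| 9 markers × 3 groups | 27 | 1.35 | 75% |
| 15 analytes × 3 groups | 45 | 2.25 | 90% |
| 15 analytes × (3 groups + pooled) | 60 | 3.0 | 95% |

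Correlation leaves the expected number unchanged but lowers the last column. For k = 45, simulated pairwise correlations of 0.2, 0.3 and 0.5 within a group give 87%, 84% and 74%. The 95% is somewhat high for a further reason: the pooled test reuses the same subjects and is not independent of the group tests.

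**The case against.** The strongest reply is that a journal article condenses the plan. Missing-data handling and multiplicity rules for secondary laboratory markers are commonly left to a SAP, which is not shown. A general 0.05 level does not by itself rule out adjusted P values. This stands in part, and it is why multiplicity is only the secondary point. It does not remove the first point, because the analysis method is stated, not left open.

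It can also be said that the article never states that all four draws enter one model. That is correct. An analysis of baseline and follow-up 1 alone would keep people who miss only the 2-year draw, so the loss is conditional on the natural reading.

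A reader might infer more than the documents support:

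- **That 12% is lost at every visit.** At follow-up 3 an absent subject has no value under any method. A mixed model recovers only what earlier values can predict.
- **That the ANOVA is valid only under completely random drop-out.** It also holds when missingness depends only on arm, age and sex, which are in the model.
- **That the estimates are biased by a known amount.** The documents say nothing on how drop-out relates to marker values or differs by arm, so no size can be given.
- **That unequal visit spacing breaks the method.** Unequal spacing does not in itself violate sphericity, and standard corrections exist.
- **That chance markers are certain, or that exactly 45 tests are planned.** The six routine analytes are only reported as measured, and the count ranges from 27 to 60.

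**Conclusion.** The point holds as a worthwhile, cheap improvement to a stated method. If all four draws enter the ANOVA, 20% drop-out leaves about 257 of 321 subjects, with a standard error at follow-up 1 up to about 12% above what the data allow. Sporadic missed draws would add to this. Selection among 2-year completers is plausible, but its size is unknown.

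The multiplicity point is supporting. With 27 to 60 tests, 1.35 to 3.0 false positives are expected if no marker responds. The 75% to 95% chance of at least one rests on a global null and independence. The article does set an FDR rule where it discusses the arrays and only a flat level elsewhere, which makes the gap worth closing. It does not prove that correction was ruled out.

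Both points concern a secondary outcome. The primary outcome, analysed by logistic regression on cognitive success, is unaffected.

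**What to change.** Replace the repeated-measures ANOVA with a linear mixed model for the three follow-up values of each marker, using all available visits. Include arm, visit, arm × visit, baseline marker value, age and sex, with an unstructured covariance across visits. Baseline enters as a covariate only, not also as an outcome visit. Report the arm difference with its interval at each visit. The model is valid if missingness depends only on observed values and covariates, and the text should state that assumption.

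For the marker tests, list the markers and analyses that form the family. Then either apply the 0.05 FDR criterion already used for the arrays across that family, or label the results exploratory.

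The cost is a change of analysis wording and slightly more analysis work, with no new data. If FDR control is chosen, fewer markers will be nominally significant.

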## Discussion

This project is designed to investigate the effects of cognitive training on different groups of elderly people. As many studies indicated that non-pharmacological strategies could be an effective intervention for elderly people with and without cognitive decline [41, 42], we choose to identify the effects of interventions of cognitive training, using a multidisciplinary point of view.

The results of this project could support and have a positive impact on National Health Service in order to produce new knowledge on cognitive decline. Surely, the analysis of the relationship between clinical, biochemical and lifestyle characteristics of elderly subjects represents an integrated approach for the study of cognitive decline. Moreover, few studies compared elderly subjects with different cognitive status using a multidisciplinary approach including the analysis of biomarkers.

Previous studies evidenced the importance of identification of rehabilitation model to guide the assessment of interventions in elderly people with cognitive deficit and recognized the usefulness of a comprehensive multi-modal cognitive training, also based on lifestyle intervention and psychological support [43].

Indeed, the preliminary identification and treatment for MCI and dementia could permit to intervene by means of a non-pharmacological approach. The characteristics of subjects who obtained a success to cognitive training will be analysed in detail, taking into account also the role of biomarkers and psycho-social aspects. MCI subjects could be treated preliminarily with this intervention in order to slow the rate of conversion into dementia, with a consequent positive effect on well-being, mood status and perceived stress level. In this way, it is possible to reduce the costs related to dementia and care-giving, using primary and secondary prevention of the cognitive decline, also reducing or delaying the degree of disability and functionality. Learning mnemonic strategies used for the enhancement of cognitive functions could be a strong benefit for the elderly, to increase personal self-esteem, to live independently for a longer period of time and to allow their caregivers a better care management.

Finally, the multidisciplinary approach and the use of multidimensional assessment could allow us to determine the best way to provide an optimal management of cognitive decline. The findings of this study will provide both healthcare professionals and elderly people with an accurate and detailed knowledge of the aspects related to cognitive decline. So, it will be possible to identify some nutritional, biological and lifestyle factors that could be associated with better cognitive performance. The analysis of biomarkers involved in the onset of cognitive decline will permit the identification of the factors related to cognitive impairment and dementia. In this way, some health programmes aimed at preventing cognitive decline and/or dementia through specific interventions of healthy lifestyle and prevention strategies will be outlined on the basis of obtained findings.
